#### Secondary outcome measures

2.7.2

##### Sagittal balance parameters of the spine and pelvis

2.7.2.1

The sagittal parameters of the spine will be measured on the full-length lateral spine X-ray film with the patient in the standing position. When the patient is X-rayed, he or she will stand naturally with the knees extended, the eyes looking forward, and upper limbs folded on the chest and lifted up to 45°.

##### Spinal parameters (Fig. 4a)

2.7.2.2

The following spinal parameters will be measured:

Lumbar lordosis: the Cobb angle between the L1 endplate tangent and S1 sacral endplate tangentLumbar vertebral angle: the Cobb angle between the anterior edge line of L3 and the perpendicular line of the endplate of the sacrumTilt angle of the first thoracic vertebra line: the Cobb angle between the line from the center of L1 to the midpoint of the sacrum endplate and a horizontal vertical line; when L1 is in front of S1, the value is positive, and when L1 is behind S1, the value is negative.

**Figure 4 F4:**
[figure not shown]
In X-ray and MRI Image, measurements of sagittal parameters of spinopelvic alignment (A and B) and the cross sectional-area (CSA) of the erector spinae (combined liocostalis and longissimus) and the vertebral body size (VB) on the inferior endplate of L1,2,3,4,5 axial (C). LL = lumbar lordosis, LA = lumbar vertebra angle, T1T = Lumbar 1 vertebra tilt angle. PI = pelvic incidence, PT = pelvic tilt, SS = sacral slope.

##### Pelvic parameters (Fig. 4b)

2.7.2.3

The following pelvic parameters will be measured:

PI: the angle between the vertical midpoint line of the upper endplate of the sacrum and the midpoint ligature of the sacrum and bilateral femoral heads. The PI is an independent morphological and relatively constant spatial parameter.SS: the angle between the upper endplate of the sacrum and the horizontal plane. The SS is a location parameter that varies with the location of the pelvis.PT: the angle between the ligature of the upper endplate midpoint of the sacrum and the central line midpoint of the bilateral femoral heads and the vertical plane. The PT is also a position parameter. According to the formula PI = SS + PT, if the SS decreases, the PT increases and vice versa.

##### Lumbar muscularity (Fig. 4c)

2.7.2.4

MRI examinations will be performed with a Siemens MAGNETOM Skyra 3.0T scanner (Siemens Healthineers, Erlangen, Germany). For the axial view, the scanner will be aligned parallel to the inferior endplate of the vertebral body. The patients will be placed in the supine position with their legs straight and lumbar spine in a neutral posture. Fifteen 4.5-mm-thick transaxial slices will be obtained (3 slices per level) with a 0.1-mm space between each slice. T2-weighted images will then be obtained with the following imaging parameters: 4000-ms repetition time, 123-ms echo time, 438 × 224 matrix, four excitations, and 180-cm field of view.

The following parameters will be measured on the MRI scans: cross-sectional area (CSA) in units of mm^2^, which indicates the size of the multifidus and erector spinae muscles including the portions of fatty change on both sides; the vertebral body (VB) in units of mm^2^, which indicates the size of the bone; and the lumbar muscularity (LM), measured as a percentage and calculated as LM = CSA / VB × 100. The CSA, VB, and LM will be measured on images displayed and analyzed with the PiView digital image viewing software. The CSA will be outlined with a graphic cursor around the paraspinal muscles (multifidus and erector spinae) on both sides, and the VB will be measured at the lower endplate of the L1–5 levels. On both sides, the thoracolumbar fascia will be traced down laterally and anteriorly to the dorsal side of the quadratus lumborum, followed by the posterior surface of the facet and lamina and the lateral margin of the spinous process. The VB will be measured on axial T2-weighted images by constructing polygon points around the outer margins of the bone without the bony spur or disc. The LM will be calculated by dividing the CSA by the VB at the lumbar vertebral level and then multiplying by 100. The average LM will be calculated as follows: LM = (CSA_L1_ + CSA_L2_ + CSA_L3_ + CSA_L4_ + CSA_L5_) / (VB_L1_ + VB_L2_ + VB_L3_ + VB_L4_ + VB_L5_) × 100.

### Safety assessment

2.8

The project director will supervise the data collection process to assure the safety of the participants. At each visit, the participants will be required to stay in the hospital for 30 minutes after the treatment and will be asked about any adverse effects that may indicate acute adverse reactions during the study period (e.g., lower limb paralysis or cauda equina syndrome). All adverse effects will be recorded at each visit during the treatment period.

### Sample size calculation

2.9

We estimated the sample size based on the main outcome indicators, and we conducted a randomized trial of Shi-style lumbar spine manipulation combined with Daoyin therapy versus lumbar traction from March to September 2018, with 10 participants in each group. The outcome parameter was the rate of improvement in the NDI (neck disability index) score from baseline to the end of the 8-week treatment. The results showed that the rate of improvement after Shi-based lumbar spine manipulation combined with Daoyin therapy was 92.0%, while that after lumbar traction was 86.6% (*P* = .893) (α = 0.05, test efficiency 1 − β = 0.8, and equivalent standard δ = 0.2).

Because our study protocol will involve the use of a non-inferiority test, according to the number of cases in the clinical non-inferiority and equivalent tests and the equivalent standard,^[17]^ and using counting data (rates) as the outcome indicators, the following formula was used to estimate the number of patients required for this study:$$n=2\times {\left({\text{U}}_{\alpha }+{\text{U}}_{\beta }\right)}^{2}\times \text{p}(1-\text{p})/\delta^{2}$$

2 × (U_α_+ U_β_)^2^was calculated as 12.365, and N was 29.537 after substituting the above figures, and the sample size of each group was about 30 cases; according to the loss rate of 20%, the sample size of each group was 36 cases, and the ratio of treatment group and control group was 1:1, a total of 72 cases.

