#### Primary outcome measures

2.7.1

Because pain is the most common symptom in patients with LDH, we chose the VAS score as one of the primary outcome measures for evaluating low back and leg pain. The VAS is a reliable and effective pain measurement tool. It is a 100-mm horizontal line showing “no pain” on the left (score of 0) and “ most severe pain possible” on the right (score of 10). In this study, the patients will use the VAS to indicate their current pain level at rest and during the most intense exercise,^[16]^ and the VAS score will thus be determined.

The pressure pain threshold (PPT) will also be measured. The PPT refers to the pressure applied when the patient feels pain in a certain area, and it is measured in units of kg/cm^2^. More severe pain is associated with a smaller PPT; conversely, less severe pain is associated with a larger PPT. In this study, a hand-held pain meter will be used to measure the PPT in the painful area of the neck. The patient will be placed in the prone position, and the pain meter will be pressed down onto the skin within the area of measurement. When the patient feels pain, the application of pressure will be stopped, and the screen of the pain meter will show the PPT.

The final primary outcome measure will be the Oswestry disability index (ODI). The ODI consists of 2 parts and a total of 10 evaluation items. The first part assesses low back pain and related symptoms (intensity of pain, concentration, and sleep), and the second part assesses activities of daily living (personal care, heavy lifting, reading, working, driving, and entertainment). The ODI is filled out by the patients according to their own conditions. Each item has a minimum score of 0 and a maximum score of 5, with higher scores indicating more serious dysfunction.

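### The 72-patient calculation treats pilot percentages that cannot be responder proportions as binomial rates, for an NDI result after 8 weeks, so its 80% power and 0.2 margin belong to no primary outcome or planned test

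*Protocol article*

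**What the plan says.** Section 2.9 (Sample size calculation) says the size is based on the main outcome indicators. Its source is a 2018 pilot of the same two treatments, "with 10 participants in each group". It continues: "The outcome parameter was the rate of improvement in the NDI (neck disability index) score from baseline to the end of the 8-week treatment". The pilot rates are 92.0% for manipulation plus Daoyin and 86.6% for traction, followed by a printed P of .893. The design values are "α = 0.05, test efficiency 1 − β = 0.8, and equivalent standard δ = 0.2". The framework is declared ("Because our study protocol will involve the use of a non-inferiority test") and so is the data type ("using counting data (rates) as the outcome indicators"). The formula is n = 2(Uα + Uβ)² p(1 − p)/δ², which gives 29.537, taken as 30 per group. Then "according to the loss rate of 20%, the sample size of each group was 36 cases", 72 in all.

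Elsewhere in the article:

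- Section 2.7.1 names three primary outcomes: VAS, PPT in kg/cm² and the ODI score. All are scores or measurements.
- Sections 2 and 2.12 give a 4-week treatment period and assess the primaries at baseline and weeks 2, 4, 12 and 24. Section 2.3 adds Daoyin for 6 months.
- Section 2.13 analyses VAS, PPT and ODI by repeated-measures ANOVA, with P < .05 as the significance criterion and two-sided 90% confidence intervals.

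**The concern.** A sample size justifies a trial only if its outcome, variance and hypothesis are those the trial will test. Here all three appear to come from something else. The outcome is a neck index, measured after a treatment length that this trial does not use. The variance is binomial, although no binary primary outcome is defined. The margin of 0.2 is a difference in proportions and has no counterpart in VAS, PPT or ODI units.

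At stake is how the result will be read. If the trial finds no difference, or claims non-inferiority, readers will rely on the stated 80% power and 0.2 margin. If neither figure belongs to the analysed outcomes, nobody can say what such a result rules out. This is not detail left to an analysis plan: the article sets out a full calculation, and that calculation disagrees with the article's own outcome and analysis sections.

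**Working it through.** **1. Reproducing the plan's figure.** Inputs from section 2.9: α = 0.05, power 0.80, δ = 0.2, rates 0.920 and 0.866.

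- 2 × (1.645 + 0.842)² = 12.365, as printed. This is one-sided 5%; two-sided 5% would give 15.698.
- p = (0.920 + 0.866)/2 = 0.893, so p(1 − p) = 0.893 × 0.107 = 0.09555.
- n = 12.365 × 0.09555/0.04 = 29.537, as printed; rounded to 30.
- 30 × 1.2 = 36 per group; 2 × 36 = 72.

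The arithmetic is as stated. The problem lies in the inputs.

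**2. Can 92.0% and 86.6% be proportions of patients?** With 10 per arm, a proportion must be a multiple of 10%. The printed rates would be 9.2 and 8.66 patients. Pilot dropout does not explain them: no denominator from 5 to 10 gives either figure. The smallest that fit are 25 for 92.0% (23/25) and 15 for about 86.6% (13/15 = 86.67%). So they are not responder rates from this pilot. They look like average percentage improvements in a score, for which p(1 − p) is not the variance.

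**3. The printed P.** The figure .893 equals the mean rate in step 1 to three decimals. A z test of 0.920 against 0.866 with 10 per arm has standard error √(0.09555 × 2/10) = 0.138, z = 0.054/0.138 = 0.39 and two-sided P of about 0.70.

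**4. Matching the calculation to the trial.**

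| Item | Section 2.9 | Rest of the article |
|---|---|---|
| Outcome | NDI rate of improvement | VAS, PPT, ODI scores (2.7.1) |
| Treatment length | 8 weeks | 4 weeks (2, 2.12); Daoyin 6 months (2.3) |
| Visit | end of week 8 | weeks 2, 4, 12, 24 (2.12) |
| Data type | binary | continuous; no responder definition |
| Test | non-inferiority of rates, δ = 0.2 | repeated-measures ANOVA; no margin (2.13) |

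**5. Loss allowance.** 36 × 0.8 = 28.8 per arm, below the required 29.537. By the plan's own formula, power is Φ(√(28.8 × 0.04/(2 × 0.09555)) − 1.645) = Φ(2.455 − 1.645) = 79.1%. Dividing by 0.8 instead gives 29.537/0.8 = 36.9, or 37 per arm (30/0.8 = 37.5, or 38, from the rounded figure).

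**6. What the numbers support on a continuous score.** Assumptions: a two-group t test at one time point, equal SDs and 80% power; for non-inferiority, a true difference of 0. Evaluable n is taken as 29 per arm (28.8 rounded). The normal approximation to the required distance is √(2/n) × (z for α + z for power). The t-based values below are slightly larger.

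| Framework | n per arm | Normal approximation | t-based |
|---|---|---|---|
| Non-inferiority margin, one-sided 5% | 29 | √(2/29) × 2.486 = 0.65 SD | 0.66 SD |
| Non-inferiority margin, one-sided 2.5% | 29 | √(2/29) × 2.802 = 0.74 SD | 0.75 SD |
| Superiority difference, two-sided 5% | 29 | 0.74 SD | 0.75 SD |
| Superiority difference, two-sided 5% | 36 | √(2/36) × 2.802 = 0.66 SD | 0.67 SD |

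If the non-inferiority margin were 0.5 SD, power with 29 per arm would be about 59% (one-sided 5%) or 46% (one-sided 2.5%).

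**The case against.** **NDI may simply be a slip for ODI.** This is plausible. "The final primary outcome measure will be the Oswestry disability index (ODI"), and section 2.7.1 also places the PPT measurement at the neck, so neck wording seems to have been carried over. A reader might infer that the pilot or the trial concerns a neck condition. The documents do not support that, since the pilot treatments are described as lumbar. The slip would remove only the neck part of the point. The 8-week period, the impossible proportions and the missing binary outcome all remain.

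**Alpha is not wholly detached.** The formula uses one-sided 5%, and the two-sided 90% interval in section 2.13 matches that. It would go too far to say that no design value carries over. The power and the margin are what lack an outcome.

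**The mislabelled P is an inference.** Its equality with the mean rate makes it very probable that .893 is the formula's p, but the article does not say so. That the percentages are mean improvements is likewise an inference; that they are not counts out of 10 is arithmetic.

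**The SD figures are not for the planned analysis.** Repeated-measures ANOVA is not a t test at one visit. Section 2.13 also appears to plan an intention-to-treat analysis with the last value carried forward, so patients lost later would stay in it, and 28.8 describes mainly the per-protocol set. This objection stands: the figures show the order of size and do not predict the power of the planned model.

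**The loss slip is trivial.** Agreed: 79.1% against 80%. It is worth correcting only because the section must be rewritten anyway.

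**Conclusion.** The point holds. The formula was evaluated correctly, but on percentages that cannot be responder proportions, for a result at a time this trial does not observe and a data type none of its primaries has. The stated 80% power and the 0.2 margin therefore apply to no primary outcome and no planned test.

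With about 29 evaluable per arm, the trial supports a non-inferiority margin of about 0.66 SD at one-sided 5% or 0.75 SD at one-sided 2.5%. If superiority is meant, it can detect 0.75 SD at two-sided 5% (0.67 SD with all 36). These figures rest on the assumptions in step 6 of the working.

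A reader might infer that 72 patients are too few, or that 72 are enough once the text is corrected. The documents support neither reading. They give no SD for VAS, PPT or ODI and no margin on any of those scales.

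**What to change.** In section 2.9:

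- Withdraw the binomial calculation and the 80% power claim.
- Correct the label on P = .893, and correct or explain the NDI and 8-week references.
- Name one primary score and time point, and state what 72 patients deliver on it.
- Declare one framework and make sections 2.9 and 2.13 agree. If non-inferiority is kept, state the margin on that score's own scale and the one-sided level, and carry both into the analysis section. If superiority is meant, remove the non-inferiority wording and give the detectable difference.
- Convert SD units to points only with a stated and sourced SD. The article does not show that the pilot recorded VAS or ODI, and an SD from 10 patients per arm would be imprecise.
- Describe the loss allowance as 28.8 evaluable per arm.
- Do not assert that 72 is adequate unless the margin or difference, together with the SD, supports it.

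The cost is the rewording of section 2.9, a matching line in section 2.13, and a less favourable stated figure.

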## Abstract

Ninety percent of elderly patients with lumbar disc herniation (LDH) have problems with the mechanics of the spine and muscle tissue. Shi-style spine balance manipulation combined with guidance (Daoyin) of muscle and bone as an alternative therapy for LDH can tone the muscle groups around the spine and maintain optimal mechanical and static sagittal balance of the spine. This study will be performed to investigate the effect of a combination of Shi-style spine balance manipulation and Daoyin therapy on LDH in middle-aged and elderly patients. In this non-blinded, randomized controlled trial, 72 eligible patients will be randomly divided into a treatment group (Shi-style spine balance manipulation combined with Daoyin therapy) and a control group (lumbar mechanical traction). Before and after the intervention, lumbar X-ray and magnetic resonance imaging examinations will be performed to observe the sagittal balance parameters of the spine and pelvis and the lumbar muscle strength. The visual analog scale score, Oswestry disability index score, and pressure pain threshold will be evaluated at baseline and at 2, 4, 12, and 24 weeks. During the treatment period, any signs of acute adverse events, such as paralysis of the lower extremities or cauda equina syndrome, will be recorded at each visit. Although Shi-style spine manipulation combined with Daoyin therapy has been used in the treatment of LDH in middle-aged and elderly people in China for many years, there is no consensus on its effectiveness. This experiment will provide convincing evidence of the efficacy of Shi-style spine manipulation combined with Daoyin therapy in the treatment of LDH in middle-aged and elderly people.

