In one retrospective study, the sagittal balance parameters of the spine and pelvis as shown by lumbar vertebral magnetic resonance imaging (MRI) and X-ray examination were compared between 32 patients aged >50 years with LDH at L4/5 and L5/S1 and 32 asymptomatic healthy persons.^[11]^ The study showed that the degree of lumbar lordosis was smaller in patients with LDH (−43.52 ± 14.56 degrees in the LDH group and −48.3 ± 11.1 degrees in the normal group). The pelvic incidence (PI) was also smaller in patients with LDH (45.1 ± 9.6 degrees in the LDH group and 49.12 ± 10.02 degrees in the normal group). The sacral slope (SS) was smaller in patients with LDH (32.05 ± 9.40 degrees in the LDH group and 34.8 ± 7.8 degrees in the normal group), as was the pelvic tilt (PT) (10.3 ± 6.7 degrees in the LDH group and 17.53 ± 8.57 degrees in the normal group). The severity of thoracic kyphosis was greater in patients with LDH (27.6 ± 10.33 degrees in the LDH group and 24.2 ± 9.8 degrees in the normal group). At present, there is a lack of research on the parameters of spinal sagittal balance and lumbar bone structure in elderly patients with complicated LDH treated by spinal balance manipulation combined with Daoyin therapy. The above research results provide an important theoretical basis for the development of our current project, which is also a continuation of previous work. Pelvic traction is beneficial for alleviating the symptoms of nerve root compression and is a common method for treating LDH. There is no clear clinical evidence against the use of traction in the treatment of LDH. Therefore, patients in the control group of our proposed study will be mainly treated with pelvic traction.

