### Statistical analyses

2.13

Trained statisticians will use the intentionality approach for validity assessment and safety analysis. The final outcome observation method will be applied to deal with missing values. All statistical analyses will be performed using SPSS version 22.0 (IBM Corp.). Before randomization, the patients baseline characteristics will be collected as descriptive statistics, including sex, age, body mass index, duration of symptoms, and degree of LDH. The data analysis of the primary outcome will be based on the per-protocol population as a supportive analysis. The mean, standard deviation, median, quartiles, and interquartile ranges will be calculated for continuous variables, and the frequency will be calculated for categorical variables. Continuous variables with a normal distribution will be calculated by the independent-samples Student *t* test and presented as mean with standard deviation; otherwise, the data will be analyzed using non-parametric tests and expressed as median with range.

Categorical variables will be expressed as number (%) and analyzed by the χ^2^ test or Fisher exact test. Repeated-measures analysis of variance will be used to analyze the changes in the VAS score, PPT, and ODI score at different time points (baseline and weeks 1, 2, 4, 12, and 24). An independent-samples *t* test will be used to analyze the changes in lumbar lordosis, lumbar vertebral angle, tilt angle of the first thoracic vertebra line, PI, PT, SS, and LM at baseline and 24 weeks. A *P* value of <.05 will be defined as statistically significant, and two-sided 90% confidence intervals will be calculated. Missing data will be input with the last observed response carried forward for all measures using the “last-value-carried-forward” principle.

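### The 72 patients are sized for non-inferiority on a rate, but the planned analysis tests differences in continuous scores with no margin, so the stated 80% power belongs to no planned test

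*Protocol article*

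**What the plan says.** Three parts of the protocol article bear on the hypothesis.

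- **Section 2.9 (Sample size calculation)** sets the size "Because our study protocol will involve the use of a non-inferiority test", "using counting data (rates) as the outcome indicators". The inputs are α = 0.05, "test efficiency 1 − β = 0.8" and "equivalent standard δ = 0.2". The rates are 92.0% and 86.6%, from a pilot with 10 participants per group. Of that pilot it says: "The outcome parameter was the rate of improvement in the NDI (neck disability index) score from baseline to the end of the 8-week treatment".
- **Section 2.13 (Statistical analyses)** plans repeated-measures analysis of variance for VAS, PPT and ODI over time, t tests or non-parametric tests for continuous variables, and χ² or Fisher tests for categorical ones. Significance is P < .05, and "two-sided 90% confidence intervals will be calculated". A per-protocol analysis of the primary outcome is supportive.
- **The aim** is stated elsewhere. The abstract promises: "This experiment will provide convincing evidence of the efficacy of Shi-style spine manipulation combined with Daoyin therapy". Section 2 asks whether the treatment leads to improvement, and section 3 speaks of effectiveness.

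Only section 2.9 mentions non-inferiority. The primary outcomes in section 2.7.1 are VAS, PPT and ODI, all measured on continuous scales.

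**The concern.** A non-inferiority trial is decided by comparing a confidence bound with a pre-set margin on the primary outcome. A superiority trial is decided by a test of difference. The size, the interval and the permitted conclusion follow from that choice. Here the size comes from the first kind of trial, the tests from the second, and the interval width again from the first.

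Two things are at stake. First, nothing fixes what a non-significant result means. With non-inferiority and equivalence both invoked in section 2.9, P > .05 could be reported as showing that the treatments are comparable, which a test of difference cannot show. Second, a reader would take 80% as the power of the analysis in section 2.13, and it is not.

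**Working it through.** **1. Reproduce the plan's figure (section 2.9).**

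Inputs: one-sided α = 0.05 (z = 1.6449), power 0.80 (z = 0.8416), margin δ = 0.2, and p as the mean of the pilot rates, (0.920 + 0.866)/2 = 0.893.

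- Multiplier: 2 × (1.6449 + 0.8416)² = 12.365, as stated.
- n = 12.365 × 0.893 × 0.107 / 0.04 = 29.537, as stated; rounded to 30.
- 30 × 1.2 = 36 per arm, 72 in total.

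Other readings do not give the stated figure. Two-sided 5% has multiplier 15.698 and n = 37.5. Two one-sided tests for equivalence, with no true difference, give n = 40.9. The 72 patients therefore rest on a one-sided 5% non-inferiority comparison of rates and on nothing else.

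**2. Set the sizing beside the analysis.**

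| Element | Section 2.9 | Section 2.13 |
|---|---|---|
| Hypothesis | non-inferiority | difference, P < .05 |
| Outcome | improvement rate (neck disability index, 8 weeks) | VAS, PPT and ODI scores |
| Margin | 0.2 on a rate difference | none |
| Decision rule | implied: bound against margin | P value |
| Interval | one-sided 5% corresponds to two-sided 90% | two-sided 90% |

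The margin of 0.2 is a difference between two proportions. No listed primary outcome is a proportion, so the margin cannot be applied to any of them.

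**3. Interval against test.**

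A two-sided 90% interval excludes zero when |z| > 1.645. A two-sided 5% test rejects when |z| > 1.960. Any result with |z| between these values (P between .05 and .10) is non-significant while its reported interval excludes zero.

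**4. What 72 patients deliver for a test of difference in means.**

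The document gives no SD and no target difference, so the answer can only be in SD units. The assumptions are a two-group comparison at one time point, two-sided 5%, 80% power and no gain from baseline adjustment. Normal approximation: d = √(15.698/n).

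- n = 36 per arm: √(15.698/36) = 0.66; by the t distribution, 0.67 SD.
- With 20% loss, 36 × 0.8 = 28.8, or about 29 evaluable: √(15.698/29) = 0.74; by the t distribution, 0.75 SD.

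**5. What 72 patients deliver for non-inferiority on a continuous score.**

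With one-sided 5%, 80% power and truly equal means, the smallest margin is d = √(12.365/n), by the normal approximation.

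- n = 36: √(12.365/36) = 0.59 SD.
- n = 29: √(12.365/29) = 0.65 SD.

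**The case against.** The strongest defence is that the parts of a non-inferiority design are present. The 90% interval is the right one for a one-sided 5% test, the per-protocol analysis is the usual companion, and the aim in section 3 of finding out whether the treatment could be a conservative option is compatible with non-inferiority. This is correct as far as it goes. The missing part is a margin that can be applied to a listed primary outcome, together with a rule that uses it. Nor can this be left to an unseen analysis plan: section 2.13 names the tests, the threshold and the interval, and they do not fit section 2.9.

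Four stronger readings are tempting, and the document does not support them.

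- **A reader might infer that no planned result could support any claim.** A significant difference in VAS or ODI favouring the treatment group would support better efficacy than traction. The fault is that the size was not set for that test.
- **A reader might infer that traction is backed only by an absence of contrary evidence**, from "There is no clear clinical evidence against the use of traction in the treatment of LDH". The sentence just before it in the Introduction says that traction helps with nerve root symptoms and is in common use. What can be said is that no effect size for traction is given.
- **A reader might compute superiority power from the pilot rates** (about 10% at 30 per arm) and predict a non-significant trial. No superiority test on those rates is planned. Moreover, with 10 per group, 92.0% and 86.6% would be 9.2 and 8.66 patients, so they do not look like responder proportions. Nothing in the document allows a likely result to be predicted for VAS, PPT or ODI.
- **A reader might say that the non-inferiority power is overstated because P < .05 is two-sided.** The multiplier 12.365 and the 90% interval both point to one-sided 5% for that comparison, so this loss is not shown.

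**Conclusion.** The point holds. The arithmetic in section 2.9 is right for a one-sided 5% non-inferiority comparison of rates, but section 2.13 plans no such comparison. Three consequences follow from the text alone: non-inferiority cannot be concluded, because the only margin fits no listed primary outcome; a non-significant difference would not show it; and the 80% power does not describe the planned tests. The 90% intervals also disagree with two-sided 5% tests for P between .05 and .10.

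In size, the planned number gives 80% power for a difference of about 0.67 SD with 36 per arm and about 0.75 SD with 29 evaluable. These figures assume a simple comparison of two means; an analysis adjusted for baseline could do somewhat better. Whether such differences are realistic cannot be judged from the document. The hypothesis should be settled before any results are seen, since otherwise the claim could be chosen to suit them.

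**What to change.** Reconcile sections 2.9 and 2.13 on one hypothesis, in one of two ways.

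**(a) Superiority.** This fits the stated aim and the tests already planned. Name one primary outcome and time point, tested at two-sided 5% with a 95% confidence interval. Withdraw the non-inferiority basis for the size. State what 72 patients deliver: 80% power for about 0.67 SD with 36 per arm and about 0.75 SD with 29 evaluable, translated into scale points once an SD is given and sourced. State that a non-significant result will not be read as non-inferior or equivalent.

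**(b) Non-inferiority.** Set and justify a margin on a listed primary outcome. Decide by the bound of the 90% interval against that margin, in both the intention-to-treat and the per-protocol sets. Restate the power on that scale (step 5 of the working gives the margins that 72 patients can support). Limit the conclusion to non-inferiority to traction, for which the protocol asserts benefit but gives no effect size.

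**Cost.** No more patients are required. Either route is more than a wording change, however: the present basis for 72 falls away, a new justification has to be written while recruitment is under way, and the stated power will be less favourable. Route (b) also gives up the efficacy claim in the abstract.

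### The 20% loss allowance was added to the target (30 × 1.2 = 36) instead of dividing the target by 0.8, so 36 per arm does not leave the required number

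*Protocol article*

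**What the plan says.** Section 2.9 (Sample size calculation) plans on a comparison of improvement rates and states that "our study protocol will involve the use of a non-inferiority test". The design values are "α = 0.05, test efficiency 1 − β = 0.8, and equivalent standard δ = 0.2". The rates come from a pilot with 10 participants per group: 92.0% with manipulation plus Daoyin and 86.6% with traction. The multiplier 2 × (Uα + Uβ)² "was calculated as 12.365", and the formula returns 29.537, taken as about 30 per group. The loss step follows in one clause: "according to the loss rate of 20%, the sample size of each group was 36 cases". With 1:1 allocation the total is 72. Section 2.10 (Randomization and allocation) then fixes 36 patients in each arm. The inflation formula is not written out.

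**The concern.** An allowance for loss should leave the calculated number of patients once the stated fraction has dropped out. With 20% loss, 80% of those enrolled remain, so the enrolled number is the target divided by 0.8. Here the target appears to have been increased by 20% of itself. If so, three figures printed together (80% power, 20% loss, 36 per arm) cannot all be true under the formula that produced them, and a reader would credit the trial with slightly more tolerance for loss than it has.

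**Working it through.** **Inputs, all from section 2.9.** α = 0.05, power 0.80, margin δ = 0.2, pilot rates 0.920 and 0.866, loss 20%. The sidedness of α is not stated. The multiplier settles it, as shown next.

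**Reproducing the number before loss**

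- Multiplier, one-sided 5%: 2 × (z₀.₉₅ + z₀.₈₀)² = 12.365, as printed. Two-sided 5% would give 15.698, so the calculation is one-sided.
- Common rate: p = (0.920 + 0.866)/2 = 0.893. Using 0.866 alone gives n = 35.9 and 0.920 alone gives 22.8, so the mean of the two was used.
- n = 12.365 × 0.893 × 0.107 / 0.2² = 29.537, as printed, rounded up to 30.

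This step reproduces exactly.

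**Reproducing the number after loss**

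| Starting value | × 1.2 | ÷ 0.8 |
|---|---|---|
| 29.537 | 35.44, so 36 | 36.92, so 37 |
| 30 | 36.0 | 37.5, so 38 |

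The stated 36 comes only from multiplying by 1.2. Dividing by 0.8 gives 37 per arm (74 in total) or 38 per arm (76 in total).

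**What 36 per arm delivers**

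- Remaining after 20% loss: 36 × 0.8 = 28.8 per arm, below both 29.537 and 30.
- Loss that 36 can absorb: 1 − 30/36 = 16.7%, or 1 − 29.537/36 = 18.0%.

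**Power on the same formula:** Φ(√[n δ² / (2p(1 − p))] − 1.645), with 2p(1 − p) = 2 × 0.893 × 0.107 = 0.1911.

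For n = 28.8: √(28.8 × 0.04/0.1911) = 2.455; 2.455 − 1.645 = 0.810; Φ(0.810) = 79.1%.

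| Patients per arm | Power |
|---|---|
| 36 (no loss) | 86.4% |
| 30 | 80.5% |
| 29.537 | 80.0% |
| 29 (7 lost) | 79.4% |
| 28.8 (exactly 20% lost) | 79.1% |
| 28 (8 lost) | 78.1% |

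**The case against.** Four points can be made for the protocol.

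1. **Size.** Against the unrounded target the gap is 29.537 − 28.8 = 0.74 patient per arm, and about one point of power. That is well inside the uncertainty of a rate taken from 10 patients per group. This stands, and it is why the point is minor.

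2. **Analysis set.** Section 2.13 plans what reads as an intention-to-treat analysis with the last value carried forward and calls the per-protocol analysis supportive. Section 2.1.2 keeps the data of patients who withdraw. Patients lost after baseline would therefore stay in the main analysis, whose nominal size is nearer 36 (86.4% power) than 28.8. This narrows the point to patients with complete data and to the per-protocol set. It does not remove it: carrying a value forward does not restore the lost information, the per-protocol result carries weight in a non-inferiority comparison, and the protocol itself chose to allow for 20% loss.

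3. **Equal rates.** The formula assumes the same rate, 0.893, in both arms. If the pilot rates were true, with unpooled variance, the power at 28.8 per arm would be Φ((0.054 + 0.2)/√[(0.920 × 0.080 + 0.866 × 0.134)/28.8] − 1.645) = Φ(3.130 − 1.645), about 93%. That is correct, but it rests on a different assumption from the one the protocol made. The stated 80% belongs to the equal-rate formula.

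4. **Wording.** Because the step is not written out, 20% might have been meant as an add-on to the target. The text calls it a loss rate, and on the usual meaning of that term the number does not follow.

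**Conclusion.** The concern holds. On the protocol's own inputs, 36 per arm with 20% loss leaves 28.8 patients and 79.1% power, so the stated combination is wrong as written. The shortfall is 1 to 2 patients per arm (2 to 4 in total), and the loss actually covered is 16.7% to 18.0%. These figures assume one-sided 5%, a rate of 0.893 in both arms, a margin of 0.2, and power judged on the patients who remain. The slip is minor and undermines no design decision.

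**What to change.** Keep 72 patients and correct the sentence in section 2.9 to say that 36 per arm allows for about 17% loss while leaving 30 per arm. Stating about 79% power at 20% loss is also correct on this formula, but the statement of about 17% loss is cleaner. The power figure refers to an improvement rate on a neck disability index, whereas the primary outcomes in section 2.7.1 are the VAS, PPT and ODI, so refining it would lend that calculation more weight than it can bear. If the power statement is used, limit it to patients with complete data or the per-protocol set. Either change costs one sentence and makes a stated figure slightly less favourable. Recruitment, conduct and budget are unaffected.
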